### Aims

The main aim of this study will be to determine the efficacy of home-based tDCS treatment in two chronic neuropathic pain patient populations: responders and non-responders to rTMS. The hypothesis is that those patients who have previously responded to rTMS will also respond to tDCS while non-responders may not. To test this hypothesis TMS responders will be subjected to three different types of tDCS: anodal, cathodal and sham tDCS. In addition, there remains a possibility that tDCS may show efficacy even in those patients who previously have not responded to rTMS. Therefore, non-responders will be subjected to the same three modes of stimulation as responders.

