### Study design

This study will be a randomised, double-blind, double cross-over, sham-controlled trial. Three stimulation modes will be compared: anodal, cathodal and sham stimulation.

Twelve responders and 12 non-responders to rTMS will be randomly assigned to receive anodal, cathodal or sham stimulation as their first treatment session.

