#### Initial and follow-up assessments

The initial and follow-up assessments will include a record of (1) handedness (not in follow-up assessments); (2) NRS for pain, including measurements for overall daily pain severity, unpleasantness of pain and severity of paroxysmal pain attacks if present. Pain diaries will be filled out daily for 1 week at baseline and for 14 days beginning at each stimulation period [39]. (3) Health status will be assessed by the Short Form 36 Health Survey (SF-36) [39]. (4) Anxiety and depression will be assessed by the hospital anxiety and depression scale (HADS) [40], as well as (5) the mini-mental state examination [41] and (6) patient experience of equipment use, including convenience and adverse effects [39]. Patients are given contact details of medically qualified personnel to contact in case of serious side effects. These will be reported descriptively.

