### Sample size calculations

As this is a pilot study, it is based on an opportune sample of 24 patients who have previously undergone rTMS and expressed willingness to take part in the study. No formal power calculations have therefore been carried out. If, however, 8/12 responders receiving anodal tDCS report a beneficial effect [weekly mean reduction of 30% or 2 units on NRS (0–10) from tDCS] and just 2/12 of non-responders do the same, this itself would give a statistical significance of *p* = 0.036 (two-tailed Fisher’s exact test). Other results would yield important data for future studies (see below).

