### Statistical analysis

A linear mixed model will be formed with fixed effects of mode of tDCS, treatment sequence, responder group and treatment period, and the random effect as patient (nested in sequence); the model will be first fitted with the pain intensity data. All patients will be included and all pairwise comparisons will be made with the estimated contrast from this model. Secondary continuous outcome measures will be analysed in the same way as the primary endpoint. Baseline covariates will be incorporated as standard fixed effects but the sensitivity of the results to other ways of incorporating baseline information will be assessed [43]. This information will be used to inform future studies. Where required, change in pain scores pre-post each treatment period will be calculated as the difference between pain during run-in baseline and pain over 3 consecutive weeks following tDCS treatment. Analysis will be performed using Stata software (StataCorp, *Stata Statistical Software*, College Station, TX: StataCorp LP). A proportion analysis will also be carried out with patients separated into responders and non-responders and their response rated as positive (pain reduction from run-in baseline of at least 2 units on VAS 0–10, or 30%) and negative (pain relief less) and analysis carried out separately for the three different tDCS treatments.

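### The only stated test of whether tDCS response differs by rTMS group uses a dichotomised pain outcome, which gives up power that the mixed model could keep

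*Protocol article*

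**What the plan says.** The Aims section sets out a difference between two groups of patients: "The hypothesis is that those patients who have previously responded to rTMS will also respond to tDCS while non-responders may not". Under Study design, "Twelve responders and 12 non-responders to rTMS will be randomly assigned" to the order of anodal, cathodal and sham stimulation, and every patient receives all three.

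The pain data are rich. The primary outcome is mean daily pain intensity in each mode, and "Pain diaries will be filled out daily for 1 week at baseline and for 14 days beginning at each stimulation period".

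Statistical analysis describes two things:

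- A linear mixed model on pain intensity with fixed effects of mode, sequence, responder group and period, and patient as a random effect. Baseline covariates are added as fixed effects. No mode-by-responder-group term is listed.
- A supplementary proportion analysis, in which patients are split by rTMS group and have "their response rated as positive (pain reduction from run-in baseline of at least 2 units on VAS 0–10, or 30%) and negative (pain relief less"). It is done separately for each of the three modes.

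Sample size calculations illustrates this second comparison. If "8/12 responders receiving anodal tDCS report a beneficial effect" and "just 2/12 of non-responders do the same", then "this itself would give a statistical significance of" p = "0.036 (two-tailed Fisher’s exact test"). The same section calls the study a pilot on an opportune sample and says that no formal power calculation was made.

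**The concern.** A responder-group main effect measures the average pain difference between the groups over all modes, sham included. It cannot show that active stimulation works better in one group than in the other. With no interaction listed, the differential effect is examined only through the proportion analysis.

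That analysis reduces an averaged 0–10 score to two categories. For example, a patient who falls by 1.9 units from a baseline of 7 meets neither limb of the rule (2 units, or 30% of 7 = 2.1 units) and counts the same as a patient who worsens. The continuous change is already collected for every patient in every mode.

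The sample is fixed at 24, so the choice of analysis is the main remaining way to improve precision. At stake is a real differential effect going undetected, and an imprecise summary of it being handed to the next study.

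**Working it through.** **Inputs from the article.** 12 patients per rTMS group (Study design); illustrative response rates of 8/12 and 2/12, two-tailed Fisher's exact test, p = 0.036 (Sample size calculations); a cut at 2 units or 30% (Statistical analysis).

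**Assumptions, not in the article.** Two-sided alpha 0.05. For the base case, pain change is normal with the same SD in both groups.

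**1. The stated figure.** Fisher's exact test on 8 positive and 4 negative versus 2 positive and 10 negative gives two-sided p = 0.0361, which reproduces 0.036. With one fewer positive responder (7/12 versus 2/12), p = 0.089.

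**2. Power of Fisher's test on the cut outcome.** Sum the product of the two binomial probabilities, Bin(12, 8/12) and Bin(12, 2/12), over all 13 × 13 outcomes with p ≤ 0.05. Power = 0.614. The test's true size, by the same sum with a common rate, is 0.021 at 5/12 and 0.009 at 2/12, well below the nominal 0.05.

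**3. Power on the uncut change.** Under the normal model the two rates imply a standardised difference

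d = z(8/12) − z(2/12) = 0.431 − (−0.967) = 1.398.

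The two-sample t-test has df = 22, critical value 2.074 and noncentrality d / √(1/12 + 1/12) = 1.398 × √6 = 3.425. Power = 0.905. The gap is 0.905 − 0.614 = 0.29.

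**4. Where the gap comes from.** The uncorrected chi-square test on the same cut outcome has power 0.772. So 0.772 − 0.614 = 0.158 is due to Fisher's conservatism, and 0.905 − 0.772 = 0.133 to the cut.

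**5. Other rates, normal equal-SD model.**

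| Rates | Fisher | t-test | Gain |
|---|---|---|---|
| 9/12 v 2/12 | 0.783 | 0.970 | 0.19 |
| 7/12 v 2/12 | 0.431 | 0.787 | 0.36 |
| 6/12 v 2/12 | 0.268 | 0.620 | 0.35 |
| 8/12 v 4/12 | 0.264 | 0.523 | 0.26 |
| 80% v 20% | 0.812 | 0.976 | 0.16 |

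**6. Other distributions, rates held at 8/12 and 2/12.**

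- Unequal SDs: with a responder-to-non-responder SD ratio from 0.5 to 2, Welch's test has power 0.93 down to 0.75, a gain of 31 down to 14 points over 0.614.
- All-or-none response (true responders shifted by k SD, cut at the midpoint; simulation). The t-test has 0.44, 0.58, 0.64 and 0.70 for k = 2, 3, 4 and 6. Fisher has 0.28, 0.46, 0.56 and 0.61. The gain is about 8 to 16 points. At k = 6 a Wilcoxon test has about 0.55 and does not beat Fisher.

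**7. What these figures do not cover.** Steps 3 to 6 compare the groups on change within one mode. The interaction proposed below uses each patient's active-minus-sham difference. If run-in, active and sham means have equal variance σ² and a common within-patient correlation ρ, both active-minus-baseline and active-minus-sham have variance 2σ²(1 − ρ). The power is then similar, provided that the groups do not differ under sham. The article does not give the correlations, so no power is claimed for the interaction itself.

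**The case against.** The strongest case on the other side has five parts.

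- **The analysis is supplementary.** The primary outcome is continuous, the mixed model comes first, and reporting a responder proportion beside it is ordinary practice. This stands, and it limits the weight of the point: the mode comparisons are unaffected.
- **Fisher's test is not fixed as the analysis.** It is named only in the sample size illustration; Statistical analysis speaks of a proportion analysis without naming a test. This also stands. More than half of the base-case gap is due to Fisher, so a reader might infer that dichotomising alone costs about 30 points. The figures do not support that: the cut costs about 13.
- **A single headline figure is not earned.** The article gives no SD, alpha or distribution. In a trial built on responders and non-responders, an all-or-none response is plausible, and there the gain is smallest. This stands, so the size must be given as a range.
- **An interaction may sit in a fuller analysis plan.** An article can leave model detail to such a plan. But this article does list the model's fixed effects and does state how the two rTMS groups are to be compared. The point concerns that stated choice and not an omitted detail.
- **No power is claimed.** The 8/12 versus 2/12 example is a correct p-value for one hypothetical result. A reader might take it as a design assumption, or take the point as a sample size error. The text supports neither. Nor does it say that a non-significant result would be reported as no differential effect.

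**Conclusion.** The point holds as an efficiency weakness. As the article states the analyses, the differential-response hypothesis is tested only on a dichotomised outcome, although the continuous outcome is available and already modelled.

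Under the article's own 8/12 versus 2/12 example the power is 0.61 with Fisher's test and about 0.90 on the uncut change. That comparison rests on an assumed two-sided alpha of 0.05 and normal changes with equal SD. Across the rates and distributions tried, the t-test gain ran from about 8 to 35 points. The direction was the same throughout for the t-test, but not for a rank test under a widely separated all-or-none response.

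This is a modest improvement to a pilot analysis. No figure in the article is wrong.

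**What to change.** Under Statistical analysis, add a mode-by-responder-group interaction to the existing mixed model for pain intensity, with run-in baseline pain among the baseline covariates already foreseen. Report the responder-versus-non-responder difference in the anodal-minus-sham and the cathodal-minus-sham effects, each with a 95% CI. This is preferable to separate group comparisons within each mode because each patient's own sham period serves as control.

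Keep the proportions meeting the 2-unit or 30% rule as a descriptive summary by group and mode, with confidence intervals. Under Sample size calculations, label the Fisher p-value as an illustration only.

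The cost is wording and one model term with (3 − 1) × (2 − 1) = 2 degrees of freedom. No new data, visits or patients are needed. A mean difference is less directly clinical than a responder rate, which the retained proportions cover. With 24 patients the interaction estimates will still be imprecise, so the intervals should carry the interpretation.

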#### Inclusion criteria

Inclusion criteria include (1) age between 18–85 years; (2) stable analgesic medication for the prior month; (3) mean pain levels ≥4 out 10 on VAS for pain during the 1-week run-in phase, based on patient diary; (4) willingness to take part; (5) ability to consent; (6) previously had a minimum of five sessions of TMS for pain, and can be named as a “responder” or “non-responder” where the responder reports a weekly average pain reduction of 20% on an NRS of 0–10, following five rTMS sessions.

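### No stated analysis tests against sham whether the tDCS effect differs between rTMS responders and non-responders, so an anodal split such as 8/12 vs 2/12 could reflect a group difference in placebo response

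*Protocol article*

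**What the plan says.** - **Aims.** The hypothesis is that previous rTMS responders will respond to tDCS and that non-responders may not.
- **Inclusion criteria.** The groups are defined by earlier outcome: the "responder reports a weekly average pain reduction of 20% on an NRS of 0–10, following five rTMS sessions". The criterion names no sham reference.
- **Study design.** "Twelve responders and 12 non-responders to rTMS will be randomly assigned" to the mode received first. Every patient later receives all three modes. Order is randomised; responder status is not.
- **Sample size calculations.** The sample is one of opportunity: "No formal power calculations have therefore been carried out". The section then illustrates: if "8/12 responders receiving anodal tDCS report a beneficial effect" and "just 2/12 of non-responders do the same, this itself would give a statistical significance of" p = 0.036 by a two-tailed Fisher test. The sham rate is not mentioned.
- **Statistical analysis.** The mixed model has fixed effects of mode, sequence, responder group and period, with patient as a random effect, and all pairwise mode contrasts. In addition there is a proportion analysis of responders and non-responders. There, positive means a fall from run-in baseline of at least 2 units or 30%, with "analysis carried out separately for the three different tDCS treatments".

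**The concern.** The hypothesis is about effect modification: is active minus sham larger in rTMS responders than in non-responders? The mixed model as listed brings in sham, but its mode contrasts apply to both groups together. The proportion analysis separates the groups, but takes each mode on its own. Neither puts the two together.

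This matters because the grouping is itself a self-reported fall in pain after stimulation. It may pick out patients who tend to report relief after any stimulation, or whose diary scores tend to fall back from a high baseline. If that tendency persists, rTMS responders would be rated positive more often under every mode, sham included. A significant anodal table could then be taken as support for the hypothesis when sham would show the same split. A significant anodal table beside a non-significant sham table would not settle it either, because that pattern is not a test of the difference between the tables.

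**Working it through.** **1. The plan's own figure.** There are 10 positives among 24 patients, 12 per group. With those margins fixed, the chance of 8 or more positives among responders is

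[C(12,8)·C(12,2) + C(12,9)·C(12,1) + C(12,10)·C(12,0)] / C(24,10) = (32,670 + 2,640 + 66) / 1,961,256 = 0.0180.

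The distribution is symmetric, so the two-tailed p is 2 × 0.0180 = 0.0361. The stated 0.036 reproduces.

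**2. What that figure cannot distinguish.** Suppose sham also gives 8/12 and 2/12. The within-mode test then gives p = 0.036 for anodal and p = 0.036 for sham, while anodal minus sham is 0 in both groups.

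**3. How often this could happen with no tDCS effect: direct rates.** The documents give no placebo rates, so these are assumptions. The chance of Fisher p ≤ 0.05 comes from exact enumeration of two Binomial(12, rate) groups.

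| Assumed placebo rate, responders / non-responders | P(p ≤ 0.05) |
|---|---|
| 0.667 / 0.167 | 61% |
| 0.50 / 0.10 | 43% |
| 0.60 / 0.20 | 39% |
| 0.40 / 0.10 | 23% |
| 0.50 / 0.20 | 21% |
| 0.40 / 0.20 | 9% |
| 0.40 / 0.40 | 2.1% |
| 0.30 / 0.30 | 1.7% |

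**4. The same, linked to the 40% response rate that the Background reports.** Assume that percentage pain reduction after any stimulation is normal with mean m and SD s, with within-patient correlation r between rTMS and tDCS periods. An rTMS responder has a reduction of at least 20%, and a positive tDCS response is at least 30%. The 2-unit alternative is left out. A 40% responder rate fixes only (20 − m)/s = 0.25 (upper tail 40.1%). The pairs 17.5/10, 15/20 and 10/40 all satisfy this: 2.5/10 = 5/20 = 10/40 = 0.25. With c = 0.25 and k = (30 − m)/s:

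- positive rate in responders = P(Z1 ≥ c, Z2 ≥ k) / P(Z1 ≥ c)
- positive rate in non-responders = [P(Z2 ≥ k) − P(Z1 ≥ c, Z2 ≥ k)] / P(Z1 < c)

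These rates are the same under anodal and sham, because no tDCS effect is assumed. Each cell shows the two rates and then the chance that the anodal Fisher test rejects.

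| m / s | r = 0 | r = 0.3 | r = 0.5 | r = 0.7 |
|---|---|---|---|---|
| 17.5 / 10 | 11% vs 11%: 0.3% | 16% vs 7%: 1.4% | 20% vs 4%: 4.3% | 24% vs 2%: 10.5% |
| 15 / 20 | 23% vs 23%: 1.4% | 32% vs 17%: 5.5% | 38% vs 12%: 16.5% | 45% vs 7%: 40.8% |
| 10 / 40 | 31% vs 31%: 1.8% | 41% vs 24%: 7.3% | 49% vs 19%: 21.6% | 58% vs 13%: 51.5% |

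For r from 0.3 to 0.7 the range is about 1% to 51%.

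**5. Does a sham reference remove it?** In the same settings, a Fisher test on a sham-corrected response (anodal reduction minus sham reduction of at least 30 points of baseline) rejects in under 2% of trials throughout. With the rates 0.667 / 0.167 of step 3, comparing the direction of discordant anodal/sham pairs between groups rejects in about 1% or less.

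**6. What a sham reference costs.** With 8/12 responders positive on anodal, the exact McNemar test against sham gives the following. The range runs from full overlap to the least possible overlap of positive patients.

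| Sham positives | p |
|---|---|
| 1/12 | 0.016 to 0.039 |
| 2/12 | 0.031 to 0.109 |
| 4/12 | 0.125 to 0.388 |

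**The case against.** Several points on the other side are right and limit the finding.

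- **Sham is not discarded.** A reader might infer that it is. Sham is one of the three modes for which proportions are analysed, so its table is a planned output, and the mixed model compares anodal with sham using the within-patient pairing. What is missing is a formal contrast of the two tables by group.
- **The sample size does not rest on the Fisher test.** A reader might infer this too. The article bases the sample on availability, disclaims a power calculation and offers the split as an illustration. It says that the split would be significant, which is true, and does not say that this would prove efficacy over sham.
- **The analysis is supplementary.** The primary outcome is mean daily pain intensity, analysed by the mixed model.
- **The size rests on assumptions.** The 40% figure fixes one combination of mean and SD, and the correlation is unknown. The model also treats the whole rTMS response as non-specific. The extreme split itself is rarer than any significant table: with mean 15%, SD 20% and correlation 0.5, at least 8/12 together with at most 2/12 occurs in about 3.6% of trials.

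The core stands after this. The article itself specifies the model terms, the response reference and the separation by mode, and nothing so specified tests the group hypothesis against sham. Pilot status does not change what the anodal table can show.

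**Conclusion.** The concern holds in this limited form, as something that should be fixed. The stated analyses do not test whether the active-minus-sham effect differs by rTMS response group, and a significant anodal-only table would not show it. The p = 0.036 is computed correctly; the question is what it tests.

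The size is uncertain. With no tDCS effect, the anodal test rejects in about 1% to 51% of trials under the assumptions above (normal pain change, correlations 0.3 to 0.7, 40% rTMS responders, 30% criterion only). The mechanism needs placebo response to differ between the groups; with equal rates the test rejects in about 2% or less. The documents give no rates by which to choose within the range. They therefore support saying that such a split could arise from placebo tendency, but not that it probably would.

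**What to change.** 1. Add a mode-by-responder-group term to the linear mixed model, and report the anodal-minus-sham and cathodal-minus-sham contrasts by group, with the difference between groups.
2. For the binary outcome, compare within-patient anodal-vs-sham response between groups. Use a paired or mixed logistic model with mode × group, or a Fisher test on a sham-corrected response. If the latter, define the base of the 30% (for example, run-in baseline pain).
3. Report estimates with confidence intervals rather than rely on significance, because 12 per group gives little power. Within-group exact McNemar tests can be shown as description only: two separate tests do not test a group difference.
4. Restate the illustration under Sample size calculations: 8/12 vs 2/12 under anodal shows association with prior rTMS response only, and must be read against the sham counts.

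The cost is small. The crossover already supplies the paired data, and the change is a model term, one further comparison and a sentence. The price is that the sham-referenced comparison has low power and the illustration becomes less favourable.

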## Discussion

With the effectiveness of non-invasive M1 stimulation recently demonstrated there has been a call from patients to facilitate more convenient forms of this therapy. It has been in direct response to this patient lead call that the present exploration of home-based non-invasive tDCS of M1 has been devised. Self-administration of tDCS obviously has both advantages and disadvantages. While it may not confer the same accuracy and consistency as clinic-based, professionally administered stimulation sessions, it does reflect the necessity for patients to be able to administer this type of therapy in the convenience of their own home. It is recognised that there will be limitations on the ability to control timing of stimulus applications and there may be some variability in technique. However, all subjects will be thoroughly briefed in the correct positioning of electrode placement and measurements will be made against previously taken MRI scans and navigated TMS data. These measurements are transferred on to securely locating headbands that are fitted individually to each patient. Each subject is observed while placing the electrodes on a number of occasions to ensure correct technique. The study described is very much a real-world test of both the effectiveness and practicality of using tDCS in this patient population, with a method of delivery that is based on other portable home-use devices such as transcutaneous electrical nerve stimulation, which has been in use for several years, albeit with varying success. If a positive effect is demonstrated it may represent an important cost-efficient option for non-invasive motor cortex stimulation in the treatment of chronic pain.

